#### *Primary outcome measure*

Primary outcome measure is progression free survival, defined as the interval between the date of randomisation and the date of progressive disease or death of any cause, whatever occurs first. Progressive disease defined as clinical and radiological signs of recurrence (RECIST 1.1 criteria) [12] or elevated CA 125 (GCIG criteria) and radiological signs of recurrence (RECIST 1.1 criteria) [13].

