#### *Experimental arm*

Secondary cytoreductive surgery must be performed within 4 weeks after randomisation. All patients will be prepared for the possibility of a bowel stoma. Surgery is carried out under antibiotic prophylaxis. The combination of antibiotics will be according local standards. The objective of the surgical intervention is complete resection of all visible disease. The extensiveness of surgery is left to the discretion of the gynaecological oncologist. The surgical procedure should start with obtaining a peritoneal fluid sample for cytology. Patients who have at least 500 ml of peritoneal fluid at the time of laparotomy are considered positive for ascites. To gain proper insight in the tumor spread, all adhesions from any previous surgery have to be excised. This is followed by a thorough inspection and palpation of the intra-abdominal and retroperitoneal contents. The extend of tumor growth is carefully recorded in eight abdominal regions. In case of peritonitis the number of tumor deposits will be recorded. Based on this information, a plan for dissection is made. At the end of the cytoreductive procedure, the extensiveness of surgery, duration of the operation, the amount of blood loss and the amount of residual tumor is recorded. Secondary cytoreductive surgery is considered complete if there is no tumor left, optimal if the largest residual tumor is ≤ 1 cm and suboptimal if more than 1 cm residual tumor (diameter (length, width or depth) of the separate tumor depositions) is left. The first chemotherapy course should be given as soon as possible but within 6 weeks after surgery.

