### Data analysis

The results of the study will be analyzed according to the intention to treat principle. All patients will be included in the analysis and patients lost to follow-up will be regarded as censored observations. Progression free and overall survival in both treatment arms will be calculated by the Kaplan-Meier method and compared by using the log-rank test, assuming that the hazard rates in the two treatment arms are roughly proportional over time. If mortality due to surgery is unexpectedly high, resulting in proportional hazard (PH) assumptions that are not valid, the primary comparison of the treatment groups will be based on the one-year progression-free disease rates. In addition, progression free and overall survival since start therapy and after the sixth chemotherapy cycle will be compared.

To adjust for baseline covariates, we will also estimate the treatment effect by Cox’s proportional hazard (PH) regression model, given that the PH assumptions are valid. If the mortality due to surgery is unexpectedly high, resulting in PH assumptions that are not valid, progression free survival since start chemotherapy will be analyzed. At least the following baseline covariates will be considered: completeness of primary surgery, FIGO stage, ECOG performance status, age, disease free interval and CA-125 at recurrence. The significance level of the final primary analysis will be set at 0.0498, and for the interim analysis at 0.001. For all other analyses, 0.05 will be used in the report of study results.

Treatment related morbidity at 30 days after surgery will be analysed with descriptive statistics. Logistic regression will be used to study relations between clinical variables and morbidity. Toxicity after the third and sixth chemotherapy course will be evaluated by means of descriptive statistics and by using an unpaired Student’s t-test or the two-sided Mann-Whitney test for the continuous variables. Comparisons of the proportions of toxicity between the 2 arms will be done by use of a two-sided chi-square test or a two-sided Fisher’s exact test if the number of expected patients in a given category is less than five.

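### If surgical mortality breaks proportional hazards, the supportive covariate-adjusted analysis restarts its clock at chemotherapy and so leaves out the surgical deaths that triggered the switch

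*Protocol article*

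**What the plan says.** All of this is in the protocol article.

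- **Primary outcome measure:** progression-free survival (PFS) is "defined as the interval between the date of randomisation and the date of progressive disease or death of any cause, whatever occurs first".
- **Data analysis, principle and population:** "The results of the study will be analyzed according to the intention to treat principle", and "All patients will be included in the analysis and patients lost to follow-up will be regarded as censored observations".
- **Data analysis, primary comparison:** log-rank test. If surgical mortality makes proportional hazards untenable, the primary comparison moves to one-year progression-free rates.
- **Data analysis, adjusted analysis (next paragraph):** "we will also estimate the treatment effect by Cox’s proportional hazard (PH) regression model, given that the PH assumptions are valid". Under the same trigger, high surgical mortality, the paragraph continues: "resulting in PH assumptions that are not valid, progression free survival since start chemotherapy will be analyzed". The substitute is PFS counted from the start of chemotherapy.
- **Control arm and Experimental arm:** controls start chemotherapy within 4 weeks of randomisation. Experimental patients have surgery within 4 weeks of randomisation, and then: "The first chemotherapy course should be given as soon as possible but within 6 weeks after surgery".
- **Secondary outcome measures:** PFS since start of therapy, overall survival and surgery-related mortality are all listed.

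**The concern.** The trigger for the substitute is an excess of deaths from surgery. The substitute then measures time from a point that those patients never reached. Entry to the analysis becomes conditional on an event after randomisation, the first chemotherapy course, which the two arms reach by different routes and at different times. The groups compared are no longer the groups that were randomised.

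At stake is the adjusted estimate in exactly the scenario that the plan anticipates. A reader would see a covariate-adjusted treatment effect that takes no account of the main early risk of the experimental treatment. The Sample size section sets the required PFS gain against expected surgical morbidity, and an estimate that leaves out surgical deaths cannot inform that trade-off.

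**Working it through.** **1. Who can enter the substitute analysis.** Latest planned start of chemotherapy after randomisation: control 4 weeks; experimental 4 + 6 = 10 weeks. A surgical death before the first course has no time zero. A surgical death after the first course would still count. No control patient can be lost through surgical death.

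**2. The plan's own figures, to fix the simulation inputs.** Inputs from Sample size: control PFS 10 months (read as a median), experimental 15 months, hazard ratio 1.5, two-sided 0.05, power 80%, accrual 60 months, further follow-up 36 months.

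- Events (Freedman): 197.
- Event probability with uniform accrual: 1 − [exp(−36λ) − exp(−96λ)]/(60λ), λ = ln 2/median. This gives 0.980 (control) and 0.936 (experimental), mean 0.958.
- 197/0.958 = 205.6, or 103 per arm, against the stated 104.
- 208/0.9 = 232 and 208 × 1.1 = 229, against the stated 230.

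The plan's figures are reproduced closely enough to use 103 per arm and a control median of 10 months.

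**3. Why the substitute cannot see surgical deaths.** Let p be surgical mortality before chemotherapy and h the hazard ratio (control/experimental) apart from surgical deaths. With exponential times, the hazard after the new origin does not depend on how many patients were removed before it. The hazard ratio from chemotherapy start is therefore h whatever p is. From randomisation it falls as p rises.

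Large-sample check (400,000 per arm; surgery at week 4, surgical deaths within 30 days after it, chemotherapy at weeks 4 and 10), as reciprocals of the experimental/control values:

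| p | h = 1.0, from randomisation | h = 1.5, from randomisation | From chemotherapy start |
|---|---|---|---|
| 0% | 1.00 | 1.50 | h |
| 2% | 0.98 | 1.47 | h |
| 5% | 0.96 | 1.41 | h |
| 10% | 0.91 | 1.33 | h |
| 15% | 0.87 | 1.25 | h |

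**4. At trial size.** Unadjusted simulation, 103 per arm:

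| p | h | From randomisation | From chemotherapy start |
|---|---|---|---|
| 5% | 1.0 | 0.96 | 1.00 |
| 5% | 1.2 | 1.14 | 1.21 |
| 5% | 1.5 | 1.42 | 1.51 |
| 10% | 1.0 | 0.91 | 1.00 |
| 10% | 1.2 | 1.08 | 1.20 |
| 10% | 1.5 | 1.32 | 1.50 |

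A rerun for this note agreed to within about 0.01. In a net-null case (p = 10%, h = 1.1) the chance of a significant result in favour of surgery rises from about 2% to 9%. In the net-harm case (p = 10%, h = 1.0) it is about 2.6% from chemotherapy start, close to the nominal one-sided 2.5%.

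**5. The primary fallback, for contrast.** One-year PFS from randomisation in controls is 2^(−12/10) = 0.435. In the experimental arm it is about (1 − p) × 2^(−12/(10h)). For h = 1.5 this is 0.574 at p = 0 and 0.9 × 0.574 = 0.517 at p = 10%. For h = 1.0 and p = 10% it is 0.9 × 0.435 = 0.392, a deficit of about 4 percentage points. The primary fallback sees the deaths.

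**The case against.** Several points on the other side stand.

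- **It is not the primary analysis.** A reader might infer that the trial's main result would drop surgical deaths. It would not: the primary comparison has its own fallback, which keeps them if counted from randomisation as the primary outcome is.
- **The trial report would not conceal the deaths.** Surgery-related mortality is a named outcome, overall survival is compared by log-rank, and deaths with their causality go to the monitoring board every six months.
- **There is no conflict with the primary PFS definition.** That definition governs the primary outcome, and PFS since start of therapy is separately listed as a secondary outcome. The conflict is with intention to treat and the inclusion of all patients.
- **Harm is not turned into a significant benefit.** In the net-harm scenario the estimate becomes null. The inflation appears in net-null or diluted-benefit cases and is modest in the first.
- **The exclusion is not confined to one arm, and its count is soft.** At 10% mortality the model loses about 20 to 24 of 103 experimental patients and about 6 controls before the new origin. About 10 to 14 of the experimental losses are ordinary modelled events. Few of those would be recorded so early, because progression needs radiological signs and the first scheduled response CT comes before the fourth course. The article does not say that patients who progress before chemotherapy are dropped, and weeks 4 and 10 are upper limits.

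None of this rescues the rule. Surgical deaths before chemotherapy are lost whatever the exact timing, and the section offers no other adjusted estimate under that trigger.

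**Conclusion.** The concern holds for the supportive covariate-adjusted analysis, and only there. It is a stated rule that contradicts the intention-to-treat commitment in the same section, not a detail left to a later document. The contradiction follows from the text and needs no simulation.

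The size is conditional. In these scenarios the hazard ratio is overstated in favour of surgery by about 0.04 to 0.09 at 5% surgical mortality and 0.09 to 0.18 at 10%. It is about 0.02 to 0.03 at 2%, a rate that might never trigger the rule. The figures assume exponential PFS, surgical deaths before the first course, the latest permitted start times and no covariate adjustment. How often the rule would be invoked is not estimated. The reading also takes the sentence as replacing the adjusted Cox estimate, which is its natural sense where it stands.

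This should be fixed, but it does not threaten the primary result.

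**What to change.** In Data analysis, keep the covariate-adjusted treatment effect on all randomised patients, with time zero at randomisation and every death counted, whether or not hazards are proportional. If they are not, replace the adjusted Cox estimate with, for example, a covariate-adjusted one-year progression-free rate, which matches the plan's own primary fallback. An adjusted difference in restricted mean PFS from randomisation is an alternative.

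PFS since start of chemotherapy can stay, labelled as a supplementary description of patients who reached chemotherapy. It should be stated not to be a randomised comparison and not to replace the adjusted treatment effect. Reporting beside it, by arm, how many patients never reached chemotherapy and why would make the selection visible.

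The cost is a wording change and a little more analysis work. No extra patients or data are needed.

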#### *Secondary outcome measures*

Secondary outcome measures are overall survival, progression free survival since start therapy and after the sixth chemotherapy cycle, quality of life during two years after treatment (EORTC QLQ-C30 version 3.0 and QLQ-OV28, EQ-5D), surgery related morbidity and mortality, toxicity (NCI-CTC Toxicity Scale Version 4.0), tumor response following treatment (RECIST and GCIG criteria).

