### Interventions

#### *Control arm*

Patients in the control arm will receive at least six courses of platinum-containing chemotherapy. The first course should be given as soon as possible but within 4 weeks after randomisation. Chemotherapy dose and schedule, combination with other chemotherapeutic agents and pre-and post-chemotherapy medication and hydration is left to the discretion of the participating center. Before every chemotherapy cycle, hematological, renal, and hepatic function will be determined and toxicity is scored using the common toxicity criteria for adverse effects (CTCAE) version 4.0.

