### Post-treatment evaluation

In both treatment arms, evaluation of response will take place before the fourth chemotherapy course and within six weeks after the sixth chemotherapy course. This evaluation consists of determining CA 125 (GCIG criteria) and performing a CT-scan (RECIST 1.1). Toxicity is scored using the common toxicity criteria for adverse effects (CTCAE) version 4.0. Patients will be asked to fill out a quality of life questionnaire (EORTC QLQ-C30 version 3.0 and QLQ-OV28, EQ-5D). After cytoreductive surgery in the experimental arm, haemoglobin must be determined. A Case Report Form (CRF) with respect to the chemotherapeutic treatment and operation must be completed.

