#### *Assessment of serious adverse events*

A serious adverse event (SAE) related to surgery and/or chemotherapy will be collected and recorded on the Serious Adverse Event Report Form during every trial phase. They all must be reported to the principal investigator within 24 hours and will be followed until they have abated or until a stable situation has been reached.

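### Toxicity is evaluated at two course-based landmarks with no any-time or worst-grade comparison, so who reaches each landmark may select the between-arm comparison

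*Protocol article*

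**What the plan says.** Toxicity is a named secondary outcome, listed separately from surgical morbidity and mortality. Four parts of the protocol article bear on it.

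- **Data analysis, time points:** "Toxicity after the third and sixth chemotherapy course will be evaluated by means of descriptive statistics". The same sentence adds a t-test or Mann-Whitney test for continuous variables.
- **Data analysis, proportions:** "Comparisons of the proportions of toxicity between the 2 arms will be done by use of a two-sided chi-square test", with Fisher's exact test for small expected counts. This sentence gives no time point and no denominator.
- **Post-treatment evaluation, both arms:** "evaluation of response will take place before the fourth chemotherapy course and within six weeks after the sixth chemotherapy course". Within that evaluation, "Toxicity is scored using the common toxicity criteria for adverse effects (CTCAE) version 4.0".
- **Control arm:** "Before every chemotherapy cycle, hematological, renal, and hepatic function will be determined and toxicity is scored". The section on the experimental arm does not repeat this.

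The Data analysis section opens with intention to treat: "All patients will be included in the analysis and patients lost to follow-up will be regarded as censored observations".

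**The concern.** A patient has a value after the sixth course only if she received six courses. That is a post-randomisation event, and severe toxicity is one reason for not reaching it. Surgery is another possible influence. The Background says it is unknown whether secondary surgery delays chemotherapy or reduces its dose, and the Data analysis section provides for unexpectedly high surgical mortality. The latest permitted start of chemotherapy is 4 weeks after randomisation in the control arm and 4 + 6 = 10 weeks in the experimental arm.

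If early stopping differs between the arms, a comparison among patients who reach a landmark is no longer a comparison of the randomised groups. It can then make the arm with more toxicity-related stops look better tolerated than it is. The Sample size section judges the five-month target against expected surgery-related morbidity, so a reliable account of treatment burden matters when the result is interpreted.

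**Working it through.** **1. What the plan gives.** There is no toxicity rate, stopping rate or power statement for toxicity to reproduce. The only usable figures are the PFS inputs of the sample size: 10 months in the control arm (taken as a median), a five-month gain to 15, and HR 1.5. These are consistent with the stated size. Freedman's formula at 80% power and 0.05 two-sided gives 197 events. With exponential PFS, 60 months of uniform accrual and 36 months of further follow-up, the event probabilities are 0.980 and 0.936, mean 0.958. Then 197 / 0.958 = 205.6, about 103 per arm against 104 stated. For dropout, 208 / 0.9 gives 232 and 208 × 1.1 gives 229, against 230 stated.

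**2. How many patients might not reach a landmark through progression or death.** The share with a PFS event by time t is 1 − 2^(−t/median), where t is the start delay plus k cycles. Cycle length is left to the centre, so 3 and 4 weeks are assumed. Example, control arm, latest start, 3-week cycles, six courses: t = (28 + 126) / 30.4375 = 5.06 months, and 1 − 2^(−5.06/10) = 29.6%.

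| Assumed cycle and start | Event before end of course 3, control / experimental | Event before end of course 6, control / experimental |
|---|---|---|
| 3 weeks, latest permitted start | 18.7% / 18.3% | 29.6% / 25.7% |
| 4 weeks, latest permitted start | 22.5% / 20.8% | 36.0% / 30.3% |
| 3 weeks, start at 0 (control) and 5 weeks (experimental) | 13.4% / 13.8% | 24.9% / 21.7% |

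These are rough upper indications for progression and death, because a constant hazard probably overstates progression during chemotherapy. Stops for toxicity would add to them. They suggest that the group may not be small. They do not show that more patients stop early in the experimental arm.

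**3. What differential stopping would do.** All rates here are assumed. Let p be the true any-time toxicity rate and s the share who stop early, all because of toxicity. Among patients reaching the landmark the observed rate is (p − s) / (1 − s).

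- 45% versus 35%, stops 10% versus 3%: 0.35 / 0.90 = 38.9% and 0.32 / 0.97 = 33.0%. The gap falls from 10 to 5.9 points.
- 40% in both arms, stops 12% versus 4%: 0.28 / 0.88 = 31.8% and 0.36 / 0.96 = 37.5%. A false difference favours the arm with more stops.
- 55% versus 40%, stops 20% versus 10%: 0.35 / 0.80 = 43.8% and 0.30 / 0.90 = 33.3%. The gap falls from 15 to 10.4 points. With 230 / 2 = 115 per arm, normal-approximation power falls from 63% to 32%.
- 55% versus 40%, stops 10% in both: 0.45 / 0.90 = 50.0% and 0.30 / 0.90 = 33.3%. The gap is 16.7 points, so it is not diluted.

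The distortion therefore comes from unequal stopping, and its size depends wholly on rates that the article does not give.

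**4. Whether the intention-to-treat sentence supplies the missing value.** It says that all patients are included and that losses are censored. Censoring is a rule for time-to-event outcomes. It assigns no toxicity grade after the sixth course to a patient who received two courses.

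**The case against.** The strongest reply is that the exclusion is read into the text. A reader might infer that the plan drops early stoppers, but nothing in the article says so. It says that all patients are included, and toxicity after a given course can be read as toxicity accumulated up to that course. The sentence on proportions names no time point, so it is also too strong to say that the arms are compared only at the landmarks. This stands, and it limits the point to what the wording permits. It does not remove the point, because even the cumulative reading needs a rule for a patient who never reaches the course.

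A reader might also infer that per-cycle grades are collected in both arms and left unused, or conversely that the arms are scored at different intensity. Neither is established. Per-cycle scoring is written only under the control arm, but that section holds nearly all the chemotherapy detail, so the layout of a condensed article may explain the silence elsewhere.

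Safety populations and derivations are commonly left to an analysis plan or full protocol. That is true of the missing denominator. The choice of landmarks, however, is stated here.

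Serious harm is also captured elsewhere: treatment-related SAEs "will be collected and recorded on the Serious Adverse Event Report Form during every trial phase", the DSMB receives deaths, treatment failures and SAEs every six months, and 30-day surgical morbidity has its own analysis. This stands, but none of it replaces the between-arm CTCAE comparison. Finally, the illustrations use assumed rates, treat every stop as due to toxicity, and leave aside that the third-course summary would include patients who stop between the third and sixth course. They show a mechanism, not an estimate.

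**Conclusion.** The concern holds in a limited form. The article fixes the toxicity evaluation at two course-based landmarks and names no any-time or worst-grade comparison. Read as written, patients who stop before a landmark contribute no value at it. If stopping differs by arm, the comparison may be selected and may understate toxicity in the arm with more early stops.

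Neither the size nor the direction is known. The conclusion rests on two assumptions: that early stoppers have no value at a landmark, and that stopping for toxicity is unequal between the arms. The documents do not support the stronger statement that early stoppers are excluded by design or that the result will favour surgery. The issue concerns one secondary outcome. Sample size, type I error, the primary analysis, SAE recording and deaths are unaffected.

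**What to change.** - Base the between-arm chi-square or Fisher comparison on the worst CTCAE grade per patient over all chemotherapy courses received, with early stoppers counted at the worst grade they reached.
- Keep the third- and sixth-course summaries as descriptive, with the number of patients contributing in each arm.
- Report by arm how many patients received no course, since they have no chemotherapy grade under this definition.
- State that toxicity scoring before every cycle applies to both arms.
- Keep 30-day surgical morbidity as its own outcome. If total burden from randomisation is wanted, report it as an additional summary and do not merge it into this comparison.

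The cost is a few sentences of wording and slightly more analysis work. Per-cycle toxicity must also be recorded in the experimental arm, which the article implies but does not state. If it were not recorded there, a worst-grade comparison would rest on unequal assessment and could itself be biased, so the two changes belong together.

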## Background

Since overall survival is poor for patients with recurrent platinum-sensitive ovarian cancer, improvement of treatment is needed for these patients. Standard therapy in patients with platinum-sensitive recurrent ovarian cancer is platinum-based chemotherapy [1]. In two large prospective trials this resulted in a median overall survival of 18 and 29 months [2,3]. The recently published OCEANS trial, compared carboplatin in combination with gemcitabine+/- bevacizumab, and reported a median overall survival of 33-35 months [4]. The role of secondary debulking surgery in recurrent ovarian cancer is not clear, and current practice differs widely between institutions. Several studies, nearly all retrospective, with highly selected patients, have demonstrated a survival benefit with survival rates up to 62 months for patients undergoing complete secondary cytoreductive surgery [5]. Three studies evaluated the predictive factors to accomplish complete secondary cytoreductive surgery. The first, the Arbeitsgemeinschaft Gynäkologische Onkologie (AGO) DESKTOP I study, found three predictive factors for complete resection: good performance status, no or small volume of ascites ( <500 ml), and complete primary surgery or FIGO I/II. In these selected patients (AGO-score positive), complete resection was achieved in 79% [6]. The second, the DESKTOP II trial, prospectively validated the AGO score and confirmed a complete resection rate of 76% [7]. However in this validation study only 57% of the score-positive patients underwent a secondary debulking which may have resulted in selection-bias and subsequently reduced validation. The third study of Tian et al. developed a risk model with six predictive factors (FIGO stage, residual tumor after primary surgery, PFI (months), ECOG performance status, CA125 at recurrence (U/ml) and ascites at recurrence) [8]. This model categorizes patients as low or high risk. In the low-risk group the proportion of complete cytoreduction was 53.4% compared with 20.1% in the high-risk group. Inclusion criteria of the current study are based on predictive factors as observed in the mentioned studies. Due to the retrospective nature of most studies reporting on secondary cytoreductive surgery, information on surgery related morbidity and second line chemotherapy is scarce. If secondary cytoreductive surgery causes chemotherapy delays and/or dose reductions, is therefore unknown Bristow et al. reported peri-operative morbidity with a weighted mean of 19.2% [5] which seems comparable to morbidity in primary cytoreductive surgery [9]. Whether cytoreductive surgery in recurrent platinum-sensitive ovarian cancer is really beneficial remains questionable due to the lack of level I-II evidence [10]. Therefore, the 4^th^ ovarian cancer consensus conference in 2010 stated that randomized controlled phase 3 trials that evaluate the role of surgery in platinum-sensitive recurrent ovarian cancer should be considered as a priority [11].

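### Toxicity is evaluated after courses 3 and 6, which early stoppers do not reach, so the comparison may miss the toxicity that made them stop

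*Protocol article*

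**What the plan says.** Toxicity, graded by the NCI criteria version 4.0, is listed under Secondary outcome measures. Data analysis fixes when it is evaluated: "Toxicity after the third and sixth chemotherapy course will be evaluated by means of descriptive statistics". The same sentence adds a t-test or Mann-Whitney test for continuous variables. The next sentence turns to proportions: "Comparisons of the proportions of toxicity between the 2 arms will be done by use of a two-sided chi-square test", or Fisher's exact test where expected counts are small. That sentence names no course. The level follows from "For all other analyses, 0.05 will be used in the report of study results".

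Post-treatment evaluation sets the matching visits for both arms: "evaluation of response will take place before the fourth chemotherapy course and within six weeks after the sixth chemotherapy course". It then states: "Toxicity is scored using the common toxicity criteria for adverse effects (CTCAE) version 4.0".

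Scoring at every cycle is also described, but only under Control arm: "Before every chemotherapy cycle, hematological, renal, and hepatic function will be determined and toxicity is scored". The Experimental arm section does not repeat it.

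On the analysis population, Data analysis adopts intention to treat and says: "All patients will be included in the analysis and patients lost to follow-up will be regarded as censored observations". On whether surgery affects the chemotherapy that follows, Background says: "If secondary cytoreductive surgery causes chemotherapy delays and/or dose reductions, is therefore unknown".

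**The concern.** The evaluation points are defined by courses given, and only patients still on chemotherapy reach them. Someone who stops after course 2 has a value at neither point; someone who stops after course 4 has the first but not the second. Toxicity is a common reason for stopping, so those without a value may be those with more toxicity. A comparison among the patients who remain is not a comparison of the randomised groups.

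Unequal stopping between the arms is plausible. Only the experimental arm has an operation first, with up to six weeks from surgery to course 1, and Background treats the effect on chemotherapy delivery as an open question. If one arm loses more patients to toxicity, its rate at course 6 is pulled down further.

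This matters because harm is weighed against benefit here. The Sample size section accepts a gain of at least five months in progression-free survival in view of expected surgical morbidity, and chemotherapy toxicity is the other part of the harm side.

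**Working it through.** **Plan's own figure.** There is none to reproduce. The only sample-size calculation is for progression-free survival, and this point does not rest on it. No toxicity or stopping rate is given, so every rate below is an assumption chosen to show direction and range.

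**Illustration 1: rate by stopping status.** Assume grade 3 or worse toxicity in 70% of patients who stop before course 6 and in 30% of those who complete. With s the share stopping, the rate in all who started is s × 0.70 + (1 − s) × 0.30. The rate among those reaching course 6 is 0.30 whatever s is.

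- Surgery arm, s = 0.30: 0.30 × 0.70 + 0.70 × 0.30 = 0.42
- Surgery arm, s = 0.20: 0.20 × 0.70 + 0.80 × 0.30 = 0.38
- Control arm, s = 0.10: 0.10 × 0.70 + 0.90 × 0.30 = 0.34

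So 42% vs 34% (8 points), or 38% vs 34% (4 points), would be seen as 30% vs 30% after course 6. Completers were given the same rate in both arms, so the difference vanishes by construction. The example shows what can happen, not what is likely.

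**Illustration 2: a fixed true difference.** Assume true severe toxicity of 30% (control) and 45% (surgery), a 15-point excess. Let q be the share of patients with severe toxicity who stop before the course-6 assessment, and let 10% of the others also miss it. The rate among those assessed is p(1 − q) / [p(1 − q) + (1 − p) × 0.90].

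| q control | q surgery | Control seen | Surgery seen | Difference (points) |
|---|---|---|---|---|
| 0.20 | 0.20 | 0.24/0.87 = 27.6% | 0.36/0.855 = 42.1% | 14.5 |
| 0.40 | 0.40 | 0.18/0.81 = 22.2% | 0.27/0.765 = 35.3% | 13.1 |
| 0.20 | 0.40 | 27.6% | 35.3% | 7.7 |
| 0.20 | 0.60 | 27.6% | 0.18/0.675 = 26.7% | −0.9 |

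If the true rate is 30% in both arms and q is 0.20 vs 0.60, the rates seen are 27.6% vs 0.12/0.75 = 16.0%. The arm with more stopping then looks less toxic.

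**Reading the two together.** With equal toxicity-driven stopping, 13.1 to 14.5 of the 15 points remain. The loss is large only when such stopping differs between arms.

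**The case against.** A reader might infer that early stoppers are excluded from the toxicity analysis and that the more toxic arm will therefore look safe. The article does not support that, for these reasons:

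- **No exclusion is stated.** No toxicity denominator is given, and the general statement is that all patients are included. Toxicity after a course could mean cumulative toxicity up to it, which would fit scoring at every cycle. A safety population is commonly left to the full protocol or analysis plan.
- **The sentence on proportions names no course.** Carrying courses 3 and 6 over from the preceding sentence is natural but not stated.
- **Patients who never start chemotherapy have no chemotherapy toxicity.** Their harm is surgical. Adding them to the denominator would lower the surgery arm's rate.
- **Other safety data do not depend on reaching a course.** Surgical morbidity is described at 30 days, serious adverse events are collected in every trial phase, and deaths, treatment failures and serious adverse events in both arms go to the monitoring board.

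All four stand, and they limit the point. They do not remove it. The inclusion statement is completed by a censoring rule, which belongs to time-to-event analysis and cannot supply a score after a course never given. The other safety data do not replace a between-arm comparison of chemotherapy toxicity: surgical morbidity arises in one arm, serious events are a subset, and the article states no between-arm test for either.

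**Conclusion.** The point holds in a limited form. As written, the toxicity evaluation is tied to courses that not every patient reaches, so taken literally it is conditional on an event after randomisation that toxicity can cause. Whether this distorts the result depends on toxicity-driven stopping differing between arms, which the article leaves open. Its size cannot be computed from the article: under the assumed rates it runs from almost nothing to the loss of the whole difference. It concerns the comparison of chemotherapy toxicity only, and not serious adverse events, deaths or 30-day surgical morbidity. It is a worthwhile improvement to a secondary outcome and does not touch the primary analysis.

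**What to change.** In Data analysis, make the main between-arm comparison of chemotherapy toxicity each patient's worst CTCAE grade, and the proportion with any grade 3 or worse. Count from the first chemotherapy course to the post-course-6 evaluation, or to the end of a fixed window after the last course given if chemotherapy stops earlier. Include all patients who started chemotherapy, by randomised arm.

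- Report 30-day surgical morbidity separately beside it, so that surgical harm and chemotherapy toxicity are not merged.
- Show per arm the numbers randomised, starting chemotherapy, and reaching courses 3 and 6. Starting chemotherapy is itself a post-randomisation event, and these counts make that visible.
- Keep the course-3 and course-6 results as supporting descriptive tables.
- Confirm that per-cycle toxicity scoring, written only under Control arm, applies in both arms. If it does not, ascertainment is unequal and that must be settled first.

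The cost is a few sentences, with no new data collection if per-cycle scoring already covers both arms. The downside is that early stoppers have shorter exposure, so the number of courses received should stand beside the rates.
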